## Abstract

**Background: **Changes in intestinal mucosal integrity and gut microbial balance occur in severe acute malnutrition (SAM), resulting in treatment failure and adverse clinical outcomes (gram-negative sepsis, diarrhoea and high case-fatality). Transient lactose intolerance, due to loss of intestinal brush border lactase, also complicates SAM, thus milk based feeds may not be optimal for nutritional rehabilitation. Since the gut epithelial barrier can be supported by short chain fatty acids, derived from microbiota fermentation by particular fermentable carbohydrates, we postulated that an energy-dense nutritional feed comprising of legume-based fermentable carbohydrates, incorporated with lactose-free versions of standard World Health Organization (WHO) F75/F100 nutritional feeds will enhance epithelial barrier function in malnourished children, reduce and promote resolution of diarrhoea and improve overall outcome.

**Methods:** We will investigate in an open-label trial in 160 Ugandan children with SAM, defined by mid-upper arm circumference <11.5cm and/or presence of kwashiorkor. Children will be randomised to a lactose-free, chickpea-enriched feed containing 2 kcal/ml, provided in quantities to match usual energy provision (experimental) or WHO standard treatment F75 (0.75 kcal/ml) and F100 (1 kcal/ml) feeds on a 1:1 basis, conducted at Mbale Regional Referral Hospital nutritional rehabilitation unit. The primary outcomes are change in MUAC at day 90 and survival to day 90. Secondary outcomes include: i) moderate to good weight gain (>5 g/kg/day), ii)
*de novo* development of diarrhoea (>3 loose stools/day), iii) time to diarrhoea resolution (if >3 loose stools/day), and iv) time to oedema resolution (if kwashiorkor) and change in intestinal biomarkers (faecal calprotectin).

**Discussion:** We hypothesize that, if introduced early in the management of malnutrition, such lactose-free, fermentable carbohydrate-based feeds, could safely and cheaply improve global outcome by reducing lactose intolerance-related diarrhoea, improving mucosal integrity and enhancing immunity, and limiting the risk of systemic infection and associated broad-spectrum antibiotic resistance.

**Registration:**
ISRCTN 10309022.

## Introduction

Severe acute malnutrition (SAM) accounts for 1.5 million deaths worldwide annually
^1^. Undernutrition, highlighted in a Lancet series
^2^, is a greatly neglected area of research despite contributing to around 60% of childhood deaths. Community-based care with ready-to-use therapeutic food for children with
*uncomplicated* malnutrition has markedly improved recovery rates; but little progress has been made for children hospitalised with SAM in whom mortality remains high
^3^. Recommended nutritional support has shown improvements in growth but these often do not translate to improving mortality and relapse rates, indicating that current strategies are not working in practice. In order to understand why current nutritional feeds have limited impact on longer-term mortality rates despite nutritional recovery, we need a new approach to understanding the complex interaction between nutrition, the gut and its associated microbiome. For example, in African children diarrhoea complicates 65% of these children and is associated with high morbidity and mortality rates (20%)
^3,
4^. SAM causes disruption of normal intestinal flora
^5^, increased turnover of vital nutrients, disruption of gut barrier function, impaired mucosal immunity and increased risk of gram negative bacteraemia
^4^, which together form a vicious cycle
^6^.

### Lactose intolerance in SAM

The current recommended formulae by WHO, initially F75 followed by F100, are milk-based feeds and their major carbohydrate source are disaccharides (a mixture of maltodextrin, sucrose and lactose), which can cause osmotic diarrhoea
^7^ since they normally are hydrolysed by disaccharidases localized at the tip of small intestinal villi. Both lactose intolerance
^8,
9^ and intestinal atrophy have been demonstrated in children with SAM
^10–
12^. Removing lactose and replacing it with better-tolerated simple carbohydrates that do not rely on brush border enzymatic activity for digestion and absorption may be highly beneficial in preventing and ameliorating diarrhoea in SAM.

### Benefits of non-digestible fermentable carbohydrates

Numerous studies have shown that intestinal mucosal integrity and gut microbial balance can be restored by inducing fermentation in the gastrointestinal tract
^13^. Fermentable carbohydrates are increasingly being investigated as potential adjuncts to improve the balance of normal gut flora and positively influence the immunological and metabolic function of the gut
^14^. Non-digestible fermentable oligosaccharides induce favourable colonic microbiota fermentation
^15^, leading to the generation of short-chain fatty acids (SCFA), which have a positive influence on gut integrity and nutritional health by improving energy yield, production of vitamins and the stimulation of gut homeostasis, including anti-pathogen activities
^16,
17^. Preliminary data collected from children with SAM by a multi-disciplinary team at Imperial College (SMIP study) involving specialists in international child health ([name]), nutrition ([name]), metabonomics ([name]) and colonic bacterial metataxonomics ([name]) suggest that there are changes in the inter-relationships of normal gut microbes, intestinal permeability, and markers of gut barrier dysfunction and immune dysregulation in SAM which effect clinical outcome (manuscript in preparation) and are therefore potential targets for intervention. 

In the MIMBLe (Modifying
Intestinal
Integrity and
Micro
biome in Severe
Malnutrition with
Legume-Based Feeds) pilot study we tested a locally made cowpea flour using a “Posho” mill, which was added to standard nutritional feeds (as in
Figure 1) (Pan African Clinical Trial Registry:
PACTR201805003381361). This small study demonstrated that the feed is well tolerated when added to the nutritional recovery programme, and increased bacterial diversity compared to standard feeds. We also demonstrated decreases in anorectic gut hormones (manuscript in preparation).

**Figure 1. f1:**
[figure not shown]
“Posho” mill grinding legumes to create flour.

### Sources of non-digestible fermentable carbohydrate

Legumes, which contain a mixture of different types of non-digestible fermentable carbohydrates, have been demonstrated to augment microbial communities that enhance SCFA production
^18^. Furthermore, these legumes form part of the traditional East African diet consumed by children
^19^ and a number of current research programmes in East Africa are expanding legume growth to improve the environmental impact of agriculture (nitrogen fixing)
^20^, meaning that this treatment will be both acceptable and readily available to local communities. One potential commonly consumed food with prebiotic effect is chickpea. Chickpea-based follow-on formulae have been explored as a potential prevention for undernutrition
^21^.

### Summary and importance

There are multiple reasons why nutritional support, at an early stage in the management of SAM, tailored towards prevention of diarrhoea and restoring gut mucosal integrity and manipulation of the gut microbiome could enhance resilience to secondary infection and morbidity during re-feeding. Legumes, through the support of microbiota networks to produce short chain fatty acids, offer a safe therapeutic adjuvant that is easily and cheaply sourced in East Africa, and other regions with a high burden of severe malnutrition. Additional removal of lactose from therapeutic feeds should reduce incidence of osmotic diarrhoea, and related morbidity.

The planned research will bring new knowledge to the field of severe malnutrition, thereby addressing a major treatment gap, which is a
*high priority research issue and a significant barrier to progress in the reduction of mortality.* The study has the potential to suggest new therapies for enhancing recovery of gut mucosal function and resilience to infection through the modulation of the gut microbiome, thereby reducing mortality and morbidity in SAM. As the interventional feed from the original MIMBLE pilot is being refined in conjunction with a specialist food company (Campden BRI), this offers an opportunity to improve the food safety profile, product utility, and further optimise the feed by removing lactose.

## Study protocol

### Justification for the study

This phase II study will be the first step in evaluating whether giving children with severe acute malnutrition an altered nutritional feed helps repair the gut and encourage the healthy microbiome, which may reduce illness or improve recovery. In the experimental arm (legume-based feed) the standard nutritional feed that all children with severe malnutrition receive routinely will be altered by removal of lactose and adding a chickpea flour. Chickpea flour contains fibre/roughage that can help encourage SCFA production leading to modulation of the gut microbiome, thereby reducing mortality and morbidity in SAM.

### Hypothesis

We hypothesize that legume-enriched, lactose-free nutrition support will improve outcomes in children with severe acute malnutrition, compared with standard nutritional rehabilitation milks as recommended by the WHO.

### Objectives

To generate additional proof supporting the hypothesis that non-digestible fermentable carbohydrate in the form of chickpea flour will have positive effects on intestinal mucosal integrity and permeability, gut inflammation, gut microbiome and clinical outcomes in children with severe acute malnutrition compared to children receiving standard nutritional feeds. Also to provide evidence that a lactose-free feed will reduce the incidence and encourage the resolution of diarrhoea, which is a major complicating factor in SAM.

### Design and methodology

The study will be conducted in Mbale Regional Referral Hospital (MRRH), Uganda. MIMBLE 2 progress at the time of writing is detailed in the ‘Study progress’ section below.

### Study design

A single-centre, open-label pilot phase II trial comparing a lactose-free, chickpea enriched feed containing 2 kcal/ml, provided in quantities to match usual energy provision (experimental) to WHO standard treatment F75 (0.75kcal/ml) and F100 (1kcal/ml) feeds randomised on a 1:1 basis.

### Study location

The study will be conducted at the Paediatric Nutrition Unit at Mbale Regional Referral Hospital, Eastern Uganda. The 17-bedded nutrition unit in Mbale admits 300 children each year with severe acute malnutrition. Most of the clinical services provided by the paediatric department are free of charge to the patients in accordance with the government policy of no cost sharing in public hospitals.

### Study population

160 children aged > 6 months to 5 years.
*Inclusion criteria:* signs of severe malnutrition one of (i) Marasmus (defined by mid-upper arm circumference (MUAC) <11.5cm) and/or Kwashiorkor (defined as symmetrical pitting oedema involving at least the feet irrespective of WHZ score or MUAC) and a guardian or parent willing/able to provide consent.
*Exclusion criteria:* children with severe acute malnutrition with a very high risk of death due to a comorbidity e.g. malignant disease or terminal illness will be excluded.

### Sample size

Mid-upper arm circumference (MUAC) has been selected as the primary criterion for nutritional recovery because it predicts mortality better and is less affected by oedema than other anthropometric measures, and is also a good index of muscle mass. A recent trial of antimicrobial prophylaxis in Kenyan children admitted with severe malnutrition baseline mean MUAC was 10.6 cm (SD 1.06) and at 90 days, 12.2 cm (SD 1.35), a mean change of 1.6 cm (SD 1.1) nutritional recovery at 90 days
^22^. The overall sample size will be 160 children which will include 80 in each study arm. From the original MIMBLE trial, safety in the study arms were comparable to the standard intervention (manuscript in preparation). As a Phase II study, this study is designed to provide adequate proof of principal that the modified nutritional feed provides clinical, physiological and biological evidence of benefit to the child in terms of nutritional rehabilitation and the predicted effect on biological markers of gut-barrier dysfunction and on the intestinal microbiota. Additionally, it will compare the safety and tolerability of the modified nutritional feed against the current standard of care. The data will thus inform the design and effect size for future pragmatic trials. Formal sample sizes were not calculated; since the study was designed to provide safety data and some indication of the likely efficacy of the modified feed compared to standard of care. We thus aimed to study 160 children in total, which is realistic given the timeframe and funding available for the study. 

### Study methods and procedures

***Screening procedure.*** Dedicated trial research nurses will be employed to conduct the study. Eligible children will be identified by the nurse and clinician on duty and registered in the eligibility screening log. A member of the trial team will then perform a structured clinical assessment of WHO anthropometric and clinical criteria to confirm severe acute malnutrition and any exclusion criteria.

Details of those fulfilling the entry criteria will be entered onto a screening form, while reasons for non-eligibility will be added to the eligibility screening log. It is anticipated that this process will take approximately 10 minutes.

***Consent.*** Prospective written, informed consent will be sought from parents or guardians of children. Parents or guardians will be given an information sheet in their usual language containing details of this pilot study. The sheet will be read aloud to those who are unable to read. Parents and guardians will be encouraged to ask questions about the trial prior to signing the consent form (
Supplementary File 1). For parents who are unable to sign the consent form, a thumbprint will be required and a witness will be required to sign the consent form.
Supplementary File 2 contains the information given to the parents/guardians of each child in the study.

***Randomisation.*** Randomisation is in permuted blocks. The sequence was generated by a data manager at KEMRI Wellcome Trust Research Programme (KWTRP), Kilifi, Kenya. This sequence was used, by a study administrator, to prepare cards with treatment allocation (standard or altered standard with chickpea flour) at the Clinical Trial Facility, KWTRP, Kilifi, Kenya. The randomisation cards were sent to MRCI, Mbale. The cards will be kept in numbered, sealed opaque envelopes, each signed across the seal. The randomisation cards are numbered consecutively and the dedicated MIMBLE clinical trial team will select the next card in the sequence ie cards will be opened in numerical order when enrolling a patient in the clinical trial.

***Study interventions.*** Children will be randomly allocated on a 1:1 basis to:

Control arm: World Health Organization recommended F75 (0.75 kcal/ml) and F100 (1 kcal/ml) feedsExperimental arm: Lactose-free, chickpea enriched feed containing 2 kcal/ml, provided in quantities to match energy provision in standard treatment.

For the control arm, children will receive the standard inpatient hospital management as per national guidelines. Briefly, children will initially receive F75 therapeutic milk at a rate of 130 ml/kg/day, provided at 4-hour intervals. When the child has stabilized (resolved hypoglycaemia, resolved hypothermia and demonstrating appetite) they will be transitioned onto F100 therapeutic milk at the same rate. The rate may be increased by 10 ml per feed, until a maximum rate of 200 ml/kg/day has been achieved. If the child is oedematous, F75 will be commenced at 100 ml/kg/day with 4-hourly feeds until stabilized (the above criteria and the resolution of oedema). When stable the child will transition to F100 formula at the same rate, and if tolerated increase to 130 ml/kg/day. If there is no indication of fluid overload, the feed may be increased by 10 ml per feed to a maximum of 200 ml/kg/day.

For the experimental arm, children will receive pre-packaged modified feeds which are lactose-free and include chickpea (gram) flour as a source of fermentable carbohydrate. The feeds contain: lactose-free skimmed milk powder (7.25%), rapeseed oil (11.5%), gram flour (10%), sugar (9%) and water. All ingredients were sourced from established EU suppliers and passed all required safety tests for human consumption as appropriate for each ingredient (contaminants, pesticides, toxins, bacterial contamination etc.). The final feed contains (per 100 ml): 200 kcal, 18 g total carbohydrate, 5.6 g protein, 12g fat, and 0.4 g resistant starch. The quantity of feed provided will match the total amounts of energy and protein that would be received in the control arm, and additional water provided to match the fluid received.

Treatment with control/experimental treatment will be for 14 days duration, followed by standard treatment outpatient as required. This includes provision of ready to use therapeutic feeds until child has recovered, defined by a weight-for-height z-score >−2. The duration of this is variable.

### Clinical management and monitoring

***Clinical monitoring.*** Clinical monitoring will be in line with standard care at a minimum of twice daily temperature and pulse oximetry.

***Anthropometric indices.*** Children will have admission their height or length measured (using a standard height meter or a dedicated length board) and daily weight and MUAC measurements until discharge performed at the same time each day. These measurements will be repeated on day 28 and day 90 (
Table 1).

**Table 1. T1:** Assessment & investigation flow chart.

Time	Adm	Day 1	Day 7	Day 28	Day 90	Discharge
Consent + patient information leaflet	X					
Anthropometry (weight, MUAC)	Daily as inpatient			X	X	X
Height	X			X	X	X
Clinical observations	Daily as inpatient			X	X	X
Fluid balance	Daily as inpatient					X
Stool Assessment	Daily as inpatient			X	X	X
24-Dietary recall	X			X	X	
Length of stay						X
**Laboratory investigations**						
Haematology	X	X	X	X	X	
Biochemistry	X	X	X	X	X	
Glucose	X	X				
Lactate	X					
Malaria test	X					
HIV testing	X					
Urine dipstick (Multi-stick)	X					
Stool microscopy	X					
**Stored samples**						
**For Metabolomics and SCFA (NMR, GC-MS)**						
Plasma		X	X	X	X	
Urine		X	X	X	X	
Stool		X	X	X	X	
**For Metataxonomics (16s rRNA)**						
Stool		X	X	X	X	
**For Intestinal Cell Injury (Faecal Calprotectin)**						
Stool		X	X	X	X	

***Stool assessment.*** Frequency and consistency of stool will be assessed daily until discharge and at day 28 and day 90.

***Dietary recall.*** Children and/or parents/guardians will be asked to complete a 24-hour multi-pass dietary recall via a structured interview to assess the nutritional intake of children on admission, day 28 and day 90 as most children will have progressed onto normal diet with additional RUTF. Intake of standard and modified feeds will be recorded daily during the inpatient episode.

***Day 28 and day 90 follow-up.*** Children will be invited to return to the hospital for a follow-up visit on day 28 and day 90 as a day case which will last approximately 2 hours. This will include a clinical review, anthropometric measurements, and the study investigations outlined above.

***Laboratory investigations.*** Following consent and randomisation, routine admission blood samples will be taken, in accordance to routine clinical practice, for the following investigations: full blood count, clinical chemistry, lactate, glucose, blood culture, malaria status and HIV status. As per WHO guidance all parents will be approached to HIV testing. HIV testing will be conducted with provision of verbal parental or guardian consent. Pre- and post-test counselling will be done in accordance with routine practice. The total admission blood sampling volume equates to 10 ml, the majority of which is for clinical purposes and only includes an extra 3 ml for plasma storage. Routine bloods will also be taken on day 7 and day 28 and day 90 which again will include an extra 3 ml for plasma storage. Plasma will be used for short chain fatty acid and metabolite analysis (
Table 1).

At admission, day 7, day 28 and day 90 stool and urine samples will be taken and be stored. The total volume of urine and stool collected across the study will be 30 ml and 30 g, respectively. Stored samples will be used for metabolite analysis (urine and stool), faecal calprotectin (stool), reducing substances (stool) and DNA extraction for 16S rRNA metataxonomics (stool).

 All stored samples will be sent to Imperial College, London to assess the following:

Intestinal cell injury, by faecal calprotectin assays.Changes in gut microbiota, by 16S rRNA analysis for species related to gut barrier function e.g.
*Bifidobacterium* and
*Lactobacillus*.Examination of changes in host and bacterial metabolic products, by nuclear magnetic resonance spectroscopy and gas chromatography–mass spectrometry.

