### Secondary outcomes

1.Clinical:a.Weight gain (moderate to good: >5 g/kg/day)b.
*De novo* development of diarrhoea (>3 loose stools/day)c.Time to diarrhoea resolution (if >3 loose stools/day)d.Time to bi-pedal oedema resolution (for those with Kwashiorkor)

2.Changes in intestinal biomarkers:a.Intestinal cell injury (faecal calprotectin)

Supportive biological and physiological data to support end points will include:

A.Anthropometric:a.Weight/height/BMIB.Microbiota:a.Percentage change in relative populations of gut microbiotaC.Metabolomics:a.Changes in generation of short chain fatty acidsb.Changes in host and microbiota metabolic productsD.Lactose intolerance:a.Evidence of stool reducing substances at baseline

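### Table 1 places the first stored plasma, urine and stool at Day 1 and the text places them at admission; if Table 1 is followed, the biomarker changes lack a reliable pre-treatment baseline

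*Protocol article*

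**What the plan says.** Table 1 of the protocol article (the assessment and investigation flow chart) has the header "Time Adm Day 1 Day 7 Day 28 Day 90 Discharge", so admission and Day 1 are separate columns. The stored-sample rows are plasma, urine and stool for metabolomics and short-chain fatty acids, stool for 16S sequencing, and stool under the block "For Intestinal Cell Injury (Faecal Calprotectin". All five leave the admission cell empty and are marked at Day 1, Day 7, Day 28 and Day 90.

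The Laboratory investigations text differs. For stool and urine it states "At admission, day 7, day 28 and day 90 stool and urine samples will be taken and be stored". For plasma it states "The total admission blood sampling volume equates to 10 ml, the majority of which is for clinical purposes and only includes an extra 3 ml"; this extra volume is the plasma to be stored, and the same amount is added at days 7, 28 and 90. It names no Day 1 sample.

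Under Secondary outcomes, faecal calprotectin is listed as a change in an intestinal biomarker. Microbiota, short-chain fatty acids and metabolic products are supportive data, also framed as changes. The one item under lactose intolerance is "Evidence of stool reducing substances at baseline", which the Laboratory investigations text runs on stored stool.

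**The concern.** A change outcome needs a starting value that allocation cannot have influenced. The admission bloods are taken after randomisation, so what makes a first sample a baseline here is that it precedes the first allocated feed. An admission sample can meet that condition. A Day 1 sample normally would not.

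If the first value is already affected by the feed, a change score subtracts whatever effect has appeared by then. Stool reducing substances raise a related problem. The section on lactose intolerance describes F75 and F100 as containing lactose, while the experimental feed has none. A stool passed after feeding starts could therefore differ by arm, although the measure is meant to describe the child before treatment.

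At stake are one listed secondary outcome and the supportive mechanistic data. Mechanistic evidence is a stated purpose of this phase II trial (Objectives; Sample size).

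**Working it through.** **1. Are admission and Day 1 the same time?** Mapping the marks to the column headers:

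| Table 1 row | Adm | Day 1 | Day 7 | Day 28 | Day 90 |
|---|---|---|---|---|---|
| Haematology | X | X | X | X | X |
| Glucose | X | X | | | |
| Stored plasma | | X | X | X | X |
| Stored stool | | X | X | X | X |

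The haematology row reads "Haematology X X X X X", which marks admission and Day 1 separately; biochemistry and glucose do likewise. The table therefore treats them as two times. Stool microscopy is marked at admission, so that column is also used for stool.

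**2. Could both initial samples be intended?** The Safety section gives 12 ml of additional blood over the study. Each stored plasma draw is 3 ml.

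- Text schedule (admission, 7, 28, 90): 4 x 3 ml = 12 ml.
- Table schedule (Day 1, 7, 28, 90): 4 x 3 ml = 12 ml.
- Both admission and Day 1: 5 x 3 ml = 15 ml.

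The stated 12 ml is reproduced with one initial draw and not with two. For plasma the schedules are alternatives, and the total does not show which is meant. For stool and urine, text and table each list four times.

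**3. How much feeding could precede a Day 1 sample?** Study interventions says for the control arm that "children will initially receive F75 therapeutic milk at a rate of 130 ml/kg/day, provided at 4-hour intervals". That is 24 h / 4 h = 6 feeds in a day. The document does not define Day 1 or time the first feed. Assuming that Day 1 is the day after admission, and that the experimental arm is fed at a similar interval, a Day 1 sample could follow anything from 0 to about 6 or more feeds.

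**4. What does a post-feed baseline do to a change score?** Let E(t) be the between-arm difference in the marker at follow-up time t, and E(1) the difference already present at the first sample.

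- First sample before any feed: randomisation makes the expected starting difference 0, so the expected difference in change is E(t) - 0 = E(t).
- First sample after feeding starts: the expected difference in change is E(t) - E(1).

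The bias is -E(1). It is zero if the feeds have done nothing by then. It shrinks the estimate if the early effect has the same sign as E(t) and is the smaller of the two. The document gives nothing from which to estimate E(1). A comparison of follow-up values at day 7, 28 or 90 estimates E(t) directly and does not involve E(1).

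**The case against.** The best reply is that this is a clerical slip. The text consistently points to admission, it mentions no Day 1 sampling even for routine bloods, and a set of marks may simply sit one column to the right. Harm arises only if staff worked from the table. That is fair as to likelihood. However, a flow chart is often the working reference for sample collection, and nothing in the article says which version governs.

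A second reply is that timing against the first feed is operational detail that a condensed article leaves to the full protocol. That also stands: the silence on timing is no finding. The contradiction between table and text is.

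Several stronger readings are tempting and are not supported:

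- A reader might infer that the baseline is contaminated as a matter of fact. Day 1 and the first-feed time are undefined, so the most one can say is that a Day 1 sample would normally follow the start of feeding.
- A reader might infer that the lactose hypothesis depends on the reducing-substances measure. It does not. The Objectives frame that hypothesis as less diarrhoea and better resolution, and the secondary outcomes on new diarrhoea and time to resolution need no stored sample.
- A reader might put a figure on a spurious baseline difference in reducing substances. The document gives no rate of lactose malabsorption, and the result would also depend on transit time and diet before admission. The measure has no row of its own in Table 1, so a Day 1 time follows only from its use of stored stool.
- A reader might assume that baseline adjustment or subgrouping by lactose intolerance is planned. The statistical analysis section specifies neither for these markers.

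**Conclusion.** The inconsistency is real and covers stored plasma, urine and stool. If Table 1 is followed, the first sample is not a reliable pre-treatment baseline for change in faecal calprotectin or for the supportive microbiota and metabolite changes, and allocation could influence stool reducing substances at baseline. This rests on one assumption, that Day 1 falls after allocated feeding has begun; the document does not state this, but the separate columns make it the natural reading.

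The direction and size of any bias cannot be computed. Change in MUAC and survival to day 90 are untouched, as are between-arm comparisons at days 7, 28 and 90 that do not use the first sample. The point is worth correcting because it alters what the biomarker outcomes measure at almost no cost, but it does not threaten the trial's main conclusions.

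**What to change.** Reconcile Table 1 with the text by moving the first mark in the five stored-sample rows from Day 1 to admission. State that the first sample is collected before the first study feed where it can be obtained without delaying care. Record the clock times of the first study feed and of each first sample. As enrolment had begun when the article was written, establish from collection records which schedule was used for children already enrolled.

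In the analysis, do not treat a first sample taken after the first feed as a pre-treatment baseline. Add a sensitivity analysis that compares arms on follow-up values without using it. Label reducing-substances results from such stools as post-feed.

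The cost is a table correction, two time fields and a sampling instruction; the 12 ml blood total does not change. The drawback is that some children will have no pre-feed stool. Those who do may differ, for example by having more diarrhoea, so the main biomarker comparison should not be restricted to them. A pre-feed stool also reflects diet before admission, so reducing substances remain an imperfect indicator of lactose intolerance even when correctly timed.
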